## TARGET SAMPLE SIZE:

Sample size was determined using the expected proportion of event / outcome in each group values of which are estimated from literature & using the formula,

n= (Z_α_ + Z_β_)^2^ [p q]

(p-q) ^2^

where Z_α_ is the z variate of alpha error i.e. a constant with value 1.96

Z_β_ i.e. a constant with value 0.84

p, q are proportions of the variable, values of which are taken from the parent article.

Approximate estimates:

1. 80% power
2. Type I error to be 5%
3. Type II error to be 20%
4. Difference in proportions between the groups to be 0.10

Substituting the values,

n= (1.96+ 0.84)^2^ [0.09)]

(0.10)^2^

n= 70.56

A minimum of **71 subjects per group** completing the study would be giving a good external validity. Since the number has to be equally divided in both the groups, **72 participants will be enrolled.**

For follow-up studies, to avoid loss by loss to follow up / attrition, kindly consider recruiting 5-25% more subjects so that even after attrition, we would be able to achieve the required minimum sample size.

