# Material & Methods

## 3.1 STUDY DESIGN

Study design is single blind, randomized clinical trial.

Of the 2 groups running in parallel, the control arm will receive conventional treatment as per IMP, while the other group will receive homoeopathic intervention along with IMP. Allocation ratio will be 1:1 through randomisation obtained from computerised random number generator.

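### The sample-size formula uses p × q where the variance of a two-group comparison belongs, and the group rates are not stated; 71 per group gives 80% power for a 0.10 difference only if one arm is essentially at 0% or 100%

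*Protocol*

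**What the plan says.** All of this stands in the protocol's section TARGET SAMPLE SIZE unless noted.

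- The section says that the calculation rests on the expected proportion with the outcome in each group, taken from the literature.
- The printed numerator is "n= (Z_α_ + Z_β_)^2^ [p q", closed by a bracket and divided by (p − q) squared.
- The symbols are explained as follows: "p, q are proportions of the variable, values of which are taken from the parent article". The article is not identified, the event is not named, and no value of p or q appears.
- The design inputs are "Type I error to be 5"%, 80% power and "Difference in proportions between the groups to be 0.10". The constants are 1.96 and 0.84.
- The substitution is "n= (1.96+ 0.84)^2^ [0.09", over 0.10 squared, giving 70.56.
- The conclusion reads "A minimum of 71 subjects per group completing the study would be giving a good external validity". The section then enrols 72 participants in total, which the synopsis splits as 36 in each arm.
- Section 3.1 fixes the allocation: "Allocation ratio will be 1:1 through randomisation obtained from computerised random number generator".

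The Statistical analysis section repeats 5% alpha and 80% power.

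**The concern.** The denominator is the squared between-group difference, set at 0.10, so p and q have to be the two group proportions. For two independent proportions the numerator should then be the sum of the two binomial variances. The product of the two rates is a different quantity and can be far smaller. The single value put in for it, 0.09, comes with no rates from which it could be checked.

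The 80% power is a stated design property of the trial. If it rests on an invalid variance term, a null result would be read as coming from an adequately powered comparison when the power may have been well below half. The defect is separate from the step from 71 per group to 72 in total: enrolling 142 would cure that step and leave this one in place.

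**Working it through.** **Inputs from the section.** Two-sided 5% ("where Z_α_ is the z variate of alpha error i.e. a constant with value 1.96"), 80% power (0.84), difference 0.10, value substituted for the numerator 0.09, allocation 1:1. The group rates are not given.

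**The plan's own figure.** (1.96 + 0.84)² × 0.09 / 0.10² = 7.84 × 0.09 / 0.01 = 70.56, rounded up to 71. It reproduces exactly, so 0.09 is the value that was used.

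**Correct formula.** With V = p1(1−p1) + p2(1−p2):

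- n per group (unpooled) = 7.84 × V / 0.10²
- power at n per group (unpooled) = Φ(0.10 / √(V/n) − 1.96)

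The pooled version, which takes the common proportion under the null hypothesis, gives slightly larger n and slightly lower power.

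**Reading 1: p and q are the two group rates, as defined.** Solving p × q = 0.09 with p − q = 0.10 gives p = (0.10 + √(0.01 + 0.36))/2 = 0.354 and q = 0.254. Then V = 0.354 × 0.646 + 0.254 × 0.746 = 0.418, not 0.09. The requirement is 7.84 × 0.418 / 0.01 ≈ 328 per group (331 pooled). Power at 71 is about 25%.

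**Reading 2: q means 1 − p, so 0.09 = 0.9 × 0.1.** The denominator then no longer fits, because p − q would be 0.80 and not 0.10. Taken as the variance of one arm, 0.09 leaves out the other arm. For 0.80 against 0.90, V = 0.16 + 0.09 = 0.25 and n = 7.84 × 0.25 / 0.01 = 196 (199 pooled). Power at 71 is 38–39%.

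**Reading 3: 0.09 is the full two-arm sum V.** With a difference of 0.10 this happens only at 0 against 0.10, or at 0.90 against 1.00, where V = 0 + 0.09. The correct unpooled formula then also gives 70.56, and power at 71 is 79–80%.

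**Range for a 0.10 difference.** Only the pair 0.254/0.354 follows from the text, by reading 1. The others are assumptions; each pair stands also for its mirror image (0.10 against 0.20 is the same as 0.80 against 0.90). Percentages are pooled / unpooled normal approximations.

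| Rates | V | n per group, unpooled / pooled | Power at 71 per group | Power at 36 per group |
|---|---|---|---|---|
| 0 vs 0.10 | 0.090 | 71 / 74 | 78.7 / 80.2% | 49.5 / 51.6% |
| 0.01 vs 0.11 | 0.108 | 85 / 88 | 71.3 / 72.8% | 43.0 / 44.7% |
| 0.05 vs 0.15 | 0.175 | 138 / 141 | 51.1 / 52.2% | 29.0 / 30.0% |
| 0.10 vs 0.20 | 0.250 | 196 / 199 | 38.4 / 39.2% | 21.8 / 22.4% |
| 0.254 vs 0.354 | 0.418 | 328 / 331 | 25.2 / 25.6% | 14.8 / 15.1% |
| 0.45 vs 0.55 | 0.495 | 389 / 392 | 22.0 / 22.3% | 13.2 / 13.4% |

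**Variants.** A one-sided 5% test, which the constant 1.96 does not imply, would still need 157 per group at 0.10 against 0.20. A continuity correction raises the number there to 219. At the boundary of 0 against 0.10 with 71 per group, exact enumeration gives 93% power for the Pearson chi-square test and 73% for Fisher's exact test. The protocol names a chi-square test in one section and an exact chi-square test in another.

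**The case against.** A reader might infer that 0.09 cannot be reconciled with a difference of 0.10, or that 71 per group could never give 80% power. The document supports neither. As a product, 0.09 fits 0.354 and 0.254. As a two-arm variance sum it fits 0 against 0.10 and 0.90 against 1.00, and there the correct formula returns the plan's own 70.56. Because the rates are withheld, no single figure can be called the true power; every row of the table except 0.254 against 0.354 is an assumption. It can also be said that power at 71 per group describes a trial nobody plans to run, since 36 per arm are to be enrolled.

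These points limit the claim without removing the defect. The boundary case requires an outcome that never occurs, or always occurs, in one arm. The protocol states no such expectation, and moving by one percentage point, to 0.01 against 0.11, already takes power at 71 down to 71–73%. No reading makes p × q the right variance term for two groups. The smaller enrolment makes the 80% claim less tenable, not more. Nor is this a detail left to an analysis plan: the protocol presents a completed calculation.

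**Conclusion.** The concern holds in a conditional form. The printed numerator is not the variance for comparing two independent proportions, and the two group rates are not stated. On the section's own definition of p and q, about 328 per group are needed and 71 per group gives about 25% power. A figure of 71 supports about 80% power for a 0.10 difference only if one arm's rate is essentially 0% or 100%. For assumed rates from 0.05 against 0.15 to 0.45 against 0.55, the requirement is about 140 to 390 per group, and power at 71 falls from about 52% to 22%. At the 36 per arm to be enrolled, power is about 13–52% over the whole range, the favourable boundary included. All this assumes a two-sided 5% test, a true difference of 0.10, equal allocation, a normal approximation and no attrition. The claim of 80% power cannot stand as written.

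**What to change.** In TARGET SAMPLE SIZE, replace the formula with n per group = (Zα + Zβ)² [p1(1−p1) + p2(1−p2)] / (p1 − p2)². Name the event being counted, the rate assumed in each arm and the source of each rate, then recompute. In that section and in Statistical analysis, replace the 80% power claim with the power, or the detectable difference, at the number actually enrolled. If the sponsor really did assume a rate of 0% or 100% in one arm, say so and justify it.

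The cost is protocol wording and one recalculation. The downside is that the stated power becomes less favourable, and the sponsor may have to choose between a larger trial and a more modest claim.

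### The sample size calculation requires 71 completers per group, but the protocol enrols 72 in total (36 per arm), so its own inputs give about 52% power, not 80%

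*Protocol*

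**What the plan says.** All the inputs are in the Protocol, section Target Sample Size. It sets 80% power and a 5% type I error, and says of Z-alpha that it "is the z variate of alpha error i.e. a constant with value 1.96". It takes "Difference in proportions between the groups to be 0.10". On the proportions it says only that "p, q are proportions of the variable, values of which are taken from the parent article"; neither value is given, and the substituted line shows a single figure of 0.09.

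The result, 70.56, is rounded up to a minimum of "71 subjects per group", counted as patients who complete the study. The following sentence begins "Since the number has to be equally divided in both the groups" and arrives at an enrolment of 72. The section closes with advice on attrition: "kindly consider recruiting 5-25% more subjects so that even after attrition" the minimum is still reached.

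The synopsis row on number of subjects gives 72, 36 in each arm, and section 3.1 (Study Design) sets 1:1 allocation. The Statistical analysis subsection that follows the sample size text repeats the 20% beta error and 80% power alongside the significance threshold.

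**The concern.** A per-group requirement and a two-arm total have been interchanged between two adjacent sentences. The synopsis rules out the harmless reading that 72 is meant per arm. The protocol therefore requires 142 completers and plans for 72 patients, while still claiming 80% power.

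The claim affects how the result will be read. A reader told that power was 80% will take a non-significant comparison as fairly strong evidence against a 0.10 difference. At 36 per arm it would be weak evidence. Because the power statement is repeated in the Statistical analysis text, the error carries from planning into interpretation.

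The attrition advice is not applied either. Even if 71 were the total, 72 would leave a margin of one patient.

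**Working it through.** **Inputs (Protocol, Target Sample Size):** Z-alpha 1.96, Z-beta 0.84, variance term 0.09, difference 0.10. Planned number per arm: 36 (synopsis).

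**1. Reproduce the stated figure.**
n = (1.96 + 0.84)² × 0.09 / 0.10² = 7.84 × 9 = 70.56, so 71. This matches. With unrounded z values it is 70.64, also 71.

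**2. Per group or total?**
As a per-group figure, the total is 2 × 71 = 142, and 72/142 = 0.51. The most favourable variant tried, a one-sided 5% test with the same variance term, gives 55.6, so 56 per group and 112 in total. No variant tried makes about 71 a two-arm total.

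**3. Power with the protocol's own formula.**
Power = Φ(√(n × 0.10² / 0.09) − 1.96)
- n = 71: 80.2%
- n = 36: √4 − 1.96 = 0.04, so 51.6%
- n = 34 (5% of 36 without a usable outcome): about 49%
- n = 27 (25% of 36 without a usable outcome): about 41%

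**4. Detectable difference at 80% power, 36 per arm, same variance term.**
(1.96 + 0.84) × √(0.09/36) = 2.8 × 0.05 = 0.14, against the 0.10 stated.

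**5. Attrition.**
Leaving 142 completers after 5% or 25% loss needs 142/0.95 = 149.5, so 150, or 142/0.75 = 189.3, so 190. Simply adding 5% to 25% to 142 gives 150 to 178.

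**6. Sensitivity to the unstated proportions (assumptions only).**
A comparison of two independent proportions has variance term v = p1(1−p1) + p2(1−p2). Required n per group is 7.84 × v / 0.01. Power at 36 per arm is Φ(0.10/√(v/36) − 1.96).

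| Assumed pair | v | n per group for 80% | Power at 36 per arm |
| --- | --- | --- | --- |
| 0.90 vs 1.00 | 0.090 | 70.6 | about 52% |
| 0.85 vs 0.95 | 0.175 | 137.2 | about 30% |
| 0.80 vs 0.90 | 0.250 | 196.0 | about 22% |
| 0.70 vs 0.80 | 0.370 | 290.1 | about 17% |
| 0.50 vs 0.60 | 0.490 | 384.2 | about 14% |

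With a 0.10 difference, v equals 0.09 only for 0.90 vs 1.00 or its mirror image, 0.10 vs 0.

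**The case against.** The contradiction itself has no good defence. The strongest replies concern what may be built on it, and most of them stand.

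- A reader might infer that non-significance is the expected result even if the assumed effect is real. The protocol's own inputs do not support that: power is 51.6%, so a significant result is marginally more likely than not. The statement needs either patients without outcomes or proportions that the protocol does not give.
- A reader might take the true power to be 14% to 22%. Those figures depend on assumed proportions. The one pair consistent with both 0.09 and a 0.10 difference returns about 52%. The lower figures are scenarios, not the protocol's power.
- A reader might conclude that 36 per arm can detect only differences above about 26 points. That holds for control proportions between 0.1 and 0.6. With the same two-sample variance it is about 24 points at a control proportion of 0.70 and about 19 at 0.80. On the protocol's variance term it is 14.
- Attrition is secondary. The protocol only asks that extra recruitment be considered, and it specifies intention-to-treat analysis of all randomised patients. The 49% and 41% figures apply only where a lost patient has no usable outcome.
- The trial is labelled Phase II, and a small trial can be justified. That does not justify claiming 80% power for it.

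**Conclusion.** The point holds. The protocol's own calculation needs 142 completers and it enrols 72, about half. On its own formula and inputs, power for a 0.10 difference is about 52% rather than 80%, and the difference detectable at 80% power is 0.14. These figures need no outside assumption beyond accepting the protocol's 0.09 term.

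That term is the most favourable case among the pairs examined. How much lower the power is cannot be settled from the protocol, because the two proportions are missing. The range of about 14% to 52% is conditional on the assumed pairs shown. The error is one of statement and should be corrected before the result is interpreted. It does not by itself show that a trial of 72 should not be run.

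**What to change.** In Target Sample Size, state that 71 per group means 142 completers in total, and reconcile that section with the synopsis. Then do one of the following.

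- **Enrol to the calculation:** at least 142 completers plus a stated attrition allowance (150 to 190 enrolled for 5% to 25% loss), with the synopsis changed to match.
- **Keep 72:** remove the 80% power and 20% beta claim from both Target Sample Size and the Statistical analysis text. State the two proportions assumed and their source. Give the power for a 0.10 difference and the detectable difference at 36 per arm computed from those proportions; on the present inputs these are about 52% and 0.14.

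If 72 is kept, also say that the between-group estimate will be reported with its 95% CI and that a non-significant result will not be read as evidence of no effect. The scale of that estimate should follow the definition of the MRI outcome. The protocol describes this outcome only as a change in condition, so a risk difference should not be presumed unless a binary response is defined.

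Keeping 72 costs protocol wording and retrieval of the proportions from the source article. The stated power becomes less favourable, and more so if the proportions lie away from 0.90 vs 1.00. Enrolling 142 or more roughly doubles recruitment.

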**Comparative evaluation of effectiveness of standard of care alone and in combination with homoeopathic treatment in COVID-19 related Rhino-orbito-cerebral Mucormycosis (ROCM): A single blind, Randomized Controlled trial**

| **Title** | Comparative evaluation of effectiveness of standard of care alone and in combination with homoeopathic treatment in COVID-19 related Rhino-orbito-cerebral Mucormycosis (ROCM): A single blind, Randomized Controlled trial |
| --- | --- |
| Short Title | *Role of adjuvant homoeopathy in COVID related ROCM* |
| Methodology/Design | Randomised control, single blind, parallel group trial |
| Study Duration | 3 months |
| Study Centre(s) | **St. George’s and JJ Hospital, Mumbai** /Any other |
| Introduction | Recently, several cases of mucormycosis in people with COVID19 have been increasingly reported world-wide, in particular from India. The primary reason that appears to be facilitating Mucorales spores to germinate in people with COVID-19 is an ideal environment of low oxygen (hypoxia), high glucose (diabetes, new-onset hyperglycemia, steroid-induced hyperglycemia), acidic medium (metabolic acidosis, diabetic ketoacidosis [DKA]), high iron levels (increased ferritins) and decreased phagocytic activity of white blood cells (WBC) due to immunosuppression (SARS-CoV-2 mediated, steroid-mediated or background comorbidities) coupled with several other shared risk factors including prolonged hospitalization with or without mechanical ventilators.^[[1]](#endnote-1)^ Use of Homoeopathy as adjuvant to Standard Treatment has helped faster and better recovery in previous fungal infection. This knowledge may be put to use, and further validated in the treatment COVID related rhino-orbito-cerebral mucormycosis. The details are given in introduction section. |
| **Objectives** | **Primary Objective**   - To evaluate the role of adjuvant homoeopathy in treatment of covid-related ROCM patients through standard parameters in respective conditions   **Secondary Objective**   - To enhance the survival of the patients hospitalized due to covid-related mucormycosis |
| **Patients and Methods** | Patients hospitalised for treatment of covid-related ROCM will be provided Homoeopathy as adjuvant treatment with standard treatment care, after informed consent in one arm, and standard treatment care alone in the other. |
| **Number of Subjects (Sample Size)** | 72 (36 each arm); explained in Section 3.7) |

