## 3.5 WITHDRAWAL OF A TRIAL PARTICIPANT:

- If the patient worsens, and mucormycosis expands beyond the range of inclusion criteria
- If the patient is in need of the ventilator support
- If the participant is unwilling to continue or turns non-compliant

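### Enrolling 72 in total against a minimum of 71 completers per group, with the advised attrition allowance left out, gives about 52% power before any loss on the protocol's own formula, not 80%

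*Protocol*

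**What the plan says.** All the sample-size figures are in the protocol's Target Sample Size section.

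- The inputs are a z for alpha of 1.96, a z for beta of 0.84, and "Difference in proportions between the groups to be 0.10". The numerator shows a variance term of 0.09. The two proportions behind it are attributed to a source article and not stated.
- The result is 70.56, rounded up to 71 "subjects per group". That minimum is expressed in patients who complete the study.
- The section then states "72 participants will be enrolled". The only reason given for the step to 72 is that the number must divide equally between two groups. The synopsis confirms the reading as a total: "72 (36 each arm); explained in Section 3.7".
- It closes with advice to "kindly consider recruiting 5-25% more subjects so that even after attrition, we would be able to achieve the required minimum sample size". No part of the protocol applies this to the 72 or names an attrition rate.

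The Statistical analysis section repeats the 80% power. Section 3.5 lists reasons for withdrawing a participant, among them "If the participant is unwilling to continue or turns non-compliant". The synopsis and the Statistical Methods section call for an intention-to-treat primary analysis of all randomised patients.

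**The concern.** Three neighbouring statements do not fit together: a minimum counted in completers per group, an enrolment fixed in total by rounding alone, and advice to recruit more so that the minimum survives attrition. If the minimum is 71 completers per group, 36 per arm falls short by about half before anyone is lost, and nothing is added for loss.

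What is at stake is how a negative result will be read. A reader told that the trial has 80% power for a difference of 0.10 will take a non-significant result as fair evidence against a difference of that size. If the real chance of detecting it is about one in two or less, that reading is not warranted.

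**Working it through.** **Inputs**, all from the Target Sample Size section unless noted: z for alpha 1.96, z for beta 0.84, difference 0.10, variance term 0.09, 72 enrolled in total; 36 per arm (synopsis); 1:1 allocation (section 3.1). The protocol gives no loss rate. The 5% to 25% used below is an assumption.

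**1. The plan's own figure.** (1.96 + 0.84)² × 0.09 / 0.10² = 7.84 × 0.09 / 0.01 = 70.56, so 71. This reproduces. The protocol labels it per group, so two groups need 2 × 71 = 142 completers.

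**2. Power at the number enrolled.** Solving the same formula for power gives Φ(√(n × 0.10² / 0.09) − 1.96), with n per group.

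- n = 71: √7.889 = 2.809, Φ(0.849) = 80.2%.
- n = 36: √4 = 2, Φ(0.04) = 51.6%.

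Taking the per-group number as a total therefore costs 80.2 − 51.6 = 28.6 points with no loss at all.

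**3. Loss of outcome data from 36 per arm.**

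| Assumed loss | Evaluable per arm | Power | Further fall (points) |
| --- | --- | --- | --- |
| 0% | 36.0 | 51.6% | – |
| 5% | 34.2 | 49.6% | 2.0 |
| 10% | 32.4 | 47.5% | 4.1 |
| 15% | 30.6 | 45.4% | 6.2 |
| 20% | 28.8 | 43.2% | 8.4 |
| 25% | 27.0 | 41.0% | 10.6 |

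**4. What the advised increase would cover.** Recruiting 5% more offsets a loss of 1 − 1/1.05 = 4.8%. Recruiting 25% more offsets 1 − 1/1.25 = 20%. On that reading the relevant rows are 5% to 20%, or about 50% to 43% power.

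**5. Does repairing one defect repair the other?**

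- Correct only to 71 per group: a 5% loss leaves 71 × 0.95 = 67.45, Φ(2.738 − 1.96) = 78.2%. A 25% loss leaves 71 × 0.75 = 53.25, Φ(2.432 − 1.96) = 68.2%. There is still no allowance.
- Apply an allowance only to the 72: 72/0.95 gives 76 and 72/0.75 gives 96 in total, or 38 to 48 per arm. Power before any loss is about 54% to 64%, still far below 80%.

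**6. Sensitivity to the 0.09.** With the usual two-sample variance p(1−p) + q(1−q), a difference of 0.10 gives 0.09 only for 90% against 100% or 0% against 10%. With q = p − 0.10 the sum is 2.2p − 2p² − 0.11, which equals 0.09 at p = 0.1 and at p = 1 and is larger in between. Power at 36 per arm without loss is then lower:

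- about 22% for 80% against 90%;
- about 15% for 25.4% against 35.4% (the pair whose product is 0.09);
- about 13% for 50% against 60%.

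Even for 90% against 100%, a pooled-variance test gives 49.5%.

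**7. Detectable difference at 80% power**, holding 0.09 fixed: 2.8 × √(0.09/36) = 0.14 with no loss, and 2.8 × √(0.09/27) = 0.16 at 25% loss. Both are optimistic, because a larger difference carries a larger variance.

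**The case against.** The strongest objection is that attrition is not what loses the 80%. This stands. Power is already about 52% with every patient evaluable, and a 5% to 25% loss removes only a further 2 to 11 points. A reader might infer from the unapplied advice that 72 patients would have been enough without dropouts. The protocol's own per-group minimum rules that out.

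Second, 5% to 25% is a recruitment increase, worded as general advice for follow-up studies, and not a predicted loss for this trial. This also stands. A reader might infer that the plan expects to lose up to a quarter of its patients, but it states no loss rate. The range in the working is an assumption.

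Third, withdrawal is not the same as a missing outcome. Under intention to treat, a non-compliant patient stays in the analysis, and patients who worsen or die reach endpoints listed in the synopsis. This stands in part: section 3.5 cannot be turned into a loss rate. But intention to treat does not supply a scan that was never taken. The primary outcome is contrast MRI, and patients discharged early are followed by telephone on days 14 and 28, so some missing scans are plausible.

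Fourth, a reader might take the step from 71 to 72 as a margin of one patient. The text does not support this, because 71 is per group and 72 is the total.

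What survives is that the section states a need for an allowance, defines its minimum in completers, and then applies nothing.

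**Conclusion.** The point holds, with the causes in the right order. The protocol requires 71 completers per group and enrols 36, so the stated 80% power is not delivered. On its own formula the figure is about 52% with no loss. The absent attrition allowance is a separate, secondary defect: an assumed 5% to 25% loss of outcome data leaves 34 to 27 evaluable patients per arm and about 50% to 41% power. Correcting the per-group error alone would leave the second defect in place.

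The figures rest on the printed 0.09, the difference of 0.10 and the z of 1.96. Because p and q are not given, 52% is close to a best case, and most other pairs 0.10 apart put it well below. The documents do not support attributing the whole shortfall to attrition, or a claim that the trial will lose any particular share of its patients.

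**What to change.** Reword the sample-size text; no extra enrolment is needed.

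- In Target Sample Size, reconcile 71 per group with 72 in total, and state p and q so that the 0.09 can be checked.
- Replace the closing advice on extra recruits with one assumed attrition rate and the evaluable number it implies per arm (for 36 enrolled, about 34 at 5% loss and 27 at 25%).
- In place of the 80% claim there and in the Statistical analysis section, give the power, or the detectable difference, at that evaluable number.

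The cost is an edit to two sections and a less favourable stated power. If the sponsor instead chose to keep 80% power on the printed inputs, holding 71 completers per group would take 71/0.95, rounded up to 75, to 71/0.75, rounded up to 95, per group (150 to 190 in total) at 5% to 25% loss. That is a separate decision, and this correction does not depend on it.
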